### Brain Outcomes

#### Brain Structure

The structural sequence is a T1-weighted 3D MPRAGE sequence (TR/TE 2300/2.98 ms, Fa 9°, FOV = 256 × 256, matrix 256 × 256, voxels 1 mm^3^, 192 slices). Regional gray matter volume was measured in the prefrontal and lateral temporal cortices, basal ganglia, and hippocampi. Cortical thickness was measured in the parietal, prefrontal, and lateral temporal cortices.

#### Brain Activations

Task-related activations associated with performing updating and inhibition tasks were examined using an interleaved simultaneous multislice (accelerator factor = 6) and echo-planar imaging (TR/TE 785/30 ms, Fa 54°, FOV 192 × 192, matrix 64 × 64, voxels 3 mm^3^, 39 slices). A letter N-back task was used to assess updating activations using a block design. Three conditions were presented pseudo-randomly for a total of 15 blocks: (1) a 0-back condition serving as a control, in which a “yes” response was required upon presentation of the letter X; (2) 1-back; and (3) 2-back conditions, in which a “yes” response was required if a given letter was identical to the one presented at the *n*-back position in the sequence; and in other cases, a “no” response was expected. A 3-color Stroop task was administered to assess activity relating to inhibition. The 3 conditions, presented across 15 blocks, were as follows: (1) neutral (a string of the letter X presented in blue, green, or red font), (2) congruent (the words “BLUE,” “GREEN,” and “RED” presented in blue, green, and red font, respectively), and (3) incongruent (these same words in a colored font that does not correspond to the significance of the word). Throughout all conditions, participants also indicated the color of the font.

### Quality Control and Data Management

All assessors and supervisors received an 8-hour training session to ensure treatment adherence and harmonize data collection. They were provided with a manual that details the procedure or training. Furthermore, the first 2 participants were tested under supervision. Data were entered at the end of each wave by the assessors, who were blinded to treatment allocation. Double data entry was used for quality control for transfer cognitive tasks with manually entered scores (ie, running span, keep track, alpha span, reading span, and verbal recall in VR task). When the study was complete, the participants were contacted by phone to answer a Likert-scale questionnaire assessing their motivation associated with the intervention they received (Multimedia Appendix 1).

### Statistical Analyses

#### Sample Size

Our aim is to recruit 90 participants in total. Given an attrition rate between 10% and 16% (see [54] for a review), there would be approximately 27 participants per condition. Assuming a significance level of α=.05, a power of 0.80, and a correlation of *r*=.50 between 3 repeated measures, the G*Power 3 software for mixed designs estimates that the sample size will provide sufficient power to detect a small to medium effect (*f*=0.15). Indeed, small to medium effect sizes correspond to those observed with similar training programs in the meta-analysis by Lampit et al [55].

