### Study Design

The study design presented in Table 1 is a randomized double-blind controlled trial where older participants are randomly assigned to 1 of 3 parallel groups: inhibition, updating, and active control. In line with prior empirical work from our team showing transfer effects following attentional control training in older adults [37], training was provided in 12 30-minute training sessions over 4 weeks. All transfer measurements were completed once by a group of younger adults who did not receive the training. This is used to assess whether training helps increase performance and brain status of older adults to the level of younger adults. Given the large number of appointments, participants were recruited and trained in 5-6 waves. The study was carried out at the Research Center of the Institut universitaire de gériatrie de Montréal (CRIUGM).

**Table 1 table1:** Study design.

Schedule of events			Study period											
			Screening, baseline, and pretest		Intervention	Posttest 1	Intervention	Posttest 2		Intervention	Posttest 3	Intervention	Posttest 4	
Timepoint			V1	V2	V3–V5	V6	V6–V8	V9	V10	V11–V13	V14	V14–V16	V17	V18

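### The stated 0.80 power at f=0.15 fits about 90 analysed participants, not the 25 to 27 completers per arm left after the plan's own attrition

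*Protocol article*

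**What the plan says.** All the inputs stand in the Sample Size paragraph of the protocol article. "Our aim is to recruit 90 participants in total". After an attrition allowance of 10% to 16%, "there would be approximately 27 participants per condition". The next sentence gives the power inputs, "Assuming a significance level of α=.05, a power of 0.80" "and a correlation of *r*=.50 between 3 repeated measures", and concludes that G*Power for mixed designs "estimates that the sample size will provide sufficient power to detect a small to medium effect", with f=0.15. The paragraph adds that effects of that class match those in a cited meta-analysis of similar training programs.

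Under Study Design, "older participants are randomly assigned to 1 of 3 parallel groups: inhibition, updating, and active control". Under Analysis of Behavioral and Brain Outcomes, efficacy on each of the two primary composites (updating and inhibition) is tested by a linear mixed model with time (PRE, POST2, POST4) crossed with training (three arms). The set analysed is everyone with at least one assessment after baseline.

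**The concern.** The paragraph applies attrition first and states power second, so a reader takes 0.80 as the power that remains after dropout. Two things do not fit. The figure of 27 per condition comes from the 10% end of the attrition range only. And the 0.80 cannot be recovered from 27 per condition for the test that compares the arms.

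At stake is how the result is read. Power for the interaction is a stated property of the trial, and a non-significant interaction will be weighed against it. If the true figure is nearer 0.7 than 0.8, and if f=0.15 corresponds to a larger between-arm gain than its label suggests, the trial is less informative about modest training effects than the paragraph implies.

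**Working it through.** **Inputs.** From Sample Size: 90 recruited, attrition 10-16%, alpha .05, r=.50, m=3 occasions, f=0.15. From Study Design: k=3 arms. Two assumptions: equal arms (consistent with a single per-condition figure) and sphericity, epsilon=1 (not stated; the most favourable value).

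**Completers.**
- 10% attrition: 90 × 0.90 = 81, and 81/3 = 27.0 per arm.
- 16% attrition: 90 × 0.84 = 75.6, and 75.6/3 = 25.2 per arm, taken as 25 (N=75).

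**Power for the time × training interaction.** G*Power's within-between formula is a noncentral F with

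lambda = f² × N × m / (1 − r) = 0.0225 × 3 / 0.5 × N = 0.135 N,

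df1 = (k − 1)(m − 1) = 4, df2 = (N − k)(m − 1) = 2(N − 3).

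| N analysed | lambda | df2 | Power at f=0.15 | f detectable at 80% |
|---|---|---|---|---|
| 90 (all recruits) | 12.15 | 174 | 0.796 | 0.151 |
| 81 (27 per arm) | 10.94 | 156 | 0.745 | 0.159 |
| 75 (25 per arm) | 10.13 | 144 | 0.706 | 0.166 |

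The plan's 0.80 is reproduced, to rounding, at N=90. The first N to reach 0.80 is 91 (lambda 12.29, power 0.801). A simulation of the 3 × 3 mixed ANOVA, 4,000 runs per setting, gave 78-80% with 30 per arm, 75% with 27 and 71-73% with 25, in line with the formula. If sphericity fails, power is lower: at N=81 it is 0.710 for epsilon 0.9 and 0.650 for epsilon 0.75.

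**Could another G*Power test be meant?** The paragraph does not name one.
- Main effect of time (same lambda, df1=2): 0.843 at N=81 and 0.812 at N=75. This exceeds 0.80 but compares no arms.
- Between-arm main effect, lambda = f² N m / [1 + (m − 1) r]: at N=81, 0.0225 × 81 × 3 / 2 = 2.73, power 0.286.

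Only the interaction is both the planned efficacy test and a match to 0.80, and the match is at N=90.

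**What f=0.15 means in SD units.** For the interaction, f is the root mean square of the nine interaction residuals (cell − arm mean − occasion mean + grand mean) divided by the common SD. The documents give no pattern of means, so these patterns are assumptions; d is the largest arm's gain over control (or over the other two arms).

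| Pattern of gains | f | d at f=0.15 |
|---|---|---|
| One arm (0, d, d), others flat | 0.222 d | 0.68 SD |
| One arm (0, d/2, d), others flat | 0.192 d | 0.78 SD |
| One arm (0, d/2, d), a second gains half as much | 0.167 d | 0.90 SD |
| One arm (0, d, d), a second (0, 0, d) | 0.272 d | 0.55 SD |

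At r=.50 the SD of a change score is √(2(1 − r)) = 1 raw SD, so these are also differences in mean change in units of the change-score SD. Under the first two patterns, a true between-arm gain of 0.5 SD has interaction power of 46% and 35% respectively at N=81.

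**The case against.** **The 0.80 is right if all 90 count.** The phrase about the sample size is not expressly tied to 81, and the planned analysis keeps anyone with one assessment after baseline. POST2 falls between sessions 6 and 7, so later dropouts still contribute to the proximal outcomes. This stands in part. The 71-74% is a complete-case figure, a floor for the behavioural outcomes at the stated attrition and epsilon=1, and should not be printed as the trial's power without that qualification. But full recovery only returns to 0.796, participants lost before POST2 add nothing on the proximal outcomes, and the paragraph does not make this argument. Neuroimaging outcomes are analysed per protocol, so the argument does not reach them.

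**The gap is modest.** It is: the detectable f moves only from 0.151 to between 0.159 and 0.166.

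**A reader might infer that f=0.15 is not small to medium at all, and that the link to the meta-analysis is wrong.** The documents do not support this. On the conventional f scale (0.10 small, 0.25 medium) 0.15 lies between the two, so the label is correct in its own metric. The SD equivalent depends on an assumed pattern, and the article gives neither the value nor the metric of the meta-analytic effect, so no mismatch can be shown.

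**A reader might also infer that a null interaction will be taken to exclude modest effects.** No passage says so. The Discussion asks for cautious interpretation, and direct comparisons with control are planned even without an interaction. Those comparisons are not well powered either: about 45% for a 0.5 SD difference in gain with 27 against 27.

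**Conclusion.** The point holds as a correction to a stated power figure. For the interaction that tests efficacy, 0.80 at f=0.15 needs about 90-91 analysed participants. The completers derived in the same paragraph give about 0.745 (27 per arm) or 0.71 (25 per arm), a shortfall of 5.5 to 9.4 percentage points. The single figure of 27 also reports only the favourable end of the attrition range. These results assume equal arms, sphericity, complete cases and that the interaction is the test being powered.

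The effect-size label is not an error. It needs a scale: for this interaction, f=0.15 is a between-arm difference in gain of about 0.68-0.78 SD if one arm differs from the other two, and 0.55-0.90 SD across all the patterns tried. It should not be read as a small-to-medium standardised difference between arms.

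**What to change.** Restate the Sample Size paragraph:
- name the time × training interaction as the test powered;
- give 25-27 completers per arm (75-81 in total) after 10-16% attrition;
- give power for f=0.15 as about 71-74% on a complete-case basis, and up to about 80% if all 90 contribute through the modified intention-to-treat mixed model;
- give the f detectable with 80% power among completers as about 0.16-0.17;
- state the SD equivalent of f=0.15 with its assumed pattern (about 0.68-0.78 SD if one arm differs from the other two; 0.55-0.90 SD under other patterns), and make any comparison with the meta-analysis on that same scale.

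The cost is wording only. Data collection ended in April 2019, so neither enrolment nor the analysis changes. The stated power becomes less favourable.

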#### Analysis of Behavioral and Brain Outcomes

We will use a modified intention-to-treat analysis of behavioral outcomes to minimize attrition-related bias, so that all participants who have completed at least one postbaseline assessment will be analyzed. The effect of training programs on the behavioral outcomes will be analyzed with linear mixed-effects models (LMMs) as this analysis makes it possible to compare performance growth between groups and is resistant to missing values. Training improvements will be tested using IES as the dependent variable with 2 separate analyses using *session* (12 levels: session 1 to session 12) *× condition* (3 levels: IES 1-back/IES 2-back/IES 3-back) for the updating training and *session* (12 levels: session 1 to session 12) *× condition* (2 levels: IES Congruent/IES Incongruent) for inhibition training. When significant interaction effects are found, pairwise comparisons will be computed within each training group (comparing performances at sessions 6 and 12 to session 1) and between training conditions at sessions 6 and 12.

Efficacy of training to improve proximal task performances will be tested at 2 separate *time* (three levels: PRE/POST2/POST4) × *training* (3 levels: inhibition/updating/general knowledge) LMMs, using inhibition and updating composite scores as dependent variables. When significant interaction effects are found, pairwise comparisons will be computed within each training group (comparing performances at POST2 and POST4 to PRE) and between training groups (comparing performances for the inhibition and updating condition to general knowledge condition) at POST2 and POST4. To reduce the statistical power cost due to multiple testing corrections and as we have a priori hypotheses, we will also conduct LMM analyses in the absence of interaction to make a direct comparison between the performances of the general knowledge training group (control active) and the updating or inhibition training groups separately.

Efficacy of training to improve complex WM will be tested in the same way with separate time-varying LMMs (5 levels: PRE/POST1/POST2/POST3/POST4) × *training* (3 levels: inhibition/updating/general knowledge) for each task (ie, reading span, alpha span, and VR composite score).

Finally, we will use a per-protocol analysis for the neuroimaging outcomes. Structural MRI images will be analyzed with FreeSurfer 6 [56] to calculate regional cortical gray matter thickness, area, and volume, in the prefrontal, parietal and temporal cortices. Subcortical volumes were segmented for basal ganglia and hippocampi. fMRI images will be preprocessed with SPM12 [57] (realignment, slice timing, coregistration, normalization, smoothing) and will be analyzed as a block design model at subject level with a fixed-effects general linear model (GLM). The GLM will use 1 regressor for each condition task convolved with a canonical hemodynamic response function. A high-pass filter of 128 seconds will be applied to remove low frequencies. Task-related activation will be analyzed using the following fMRI contrasts: [1-back > 0-back] and [2-back > 0-back] as a measure of updating at varying task loads; and [2-back > 1-back] as a measure of load-related activation for the N-back task; [congruent > neutral] as a measure of reading-related activation; and [incongruent > neutral] and [incongruent > congruent] as measures of inhibition for the Stroop task. Whole-brain analysis will help determine task-related activation and whether alternative regions are recruited throughout or after training. Mixed ANOVAs will be carried out in regions of interest using beta weights from the activation clusters and from well-documented task-related regions. We will also adopt a parametric approach analysis, in which the first-level GLM included regressor for task block with parametric modulator for WM load.

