### Procedure

After a first telephone contact to assess global eligibility, potential participants were invited to the laboratory to consent to participate in the study, complete standardized clinical and neuropsychological assessments, and the outcome measurements for the baseline (V1; see list in Table 1). A brain imaging examination for the baseline was completed the following week (V2). Eligible participants were given CAD 50 (~US $38) at each brain imaging session, for a total of CAD 150 (~US $114) for older adults and CAD 50 (~US $38) for younger adults.

Data on proximal cognitive and brain outcomes were collected at 3 timepoints: no more than 2 weeks prior to training for the baseline (PRE), between training sessions 6 and 7 (POST2), and no more than 1 week following the end of training (POST4) for the postbaseline tests. Complex WM outcomes were measured at 5 time points: (1) at PRE; (2) after the third training session (POST1), (3) at POST2, (4) after the ninth training session (POST3), and at (5) POST4. The complex WM outcomes at POST1 and POST3 were completed on the same day as a training session to reduce travel and the number of visits to the laboratory. The standard duration of the study was 8 weeks and involved 18 appointments. Participants were informed that the study must be performed without discontinuity. A postponement of up to 1 week was exceptionally authorized in the event of unforeseen circumstances. To limit the influence of the circadian rhythm on performance, training sessions and assessments were performed at similar times of day (ie, morning or afternoon) for a given participant. In addition, at the end of the first appointment, a personalized calendar containing all dates and durations of appointments was given to each participant in paper format. A reminder email (or a phone call made if no email address was available) was also sent the day before each MRI appointment.

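### The behavioural analysis set leaves out randomised participants who have only a baseline score, although the planned mixed model can use them; the likely bias is small and the remedy is free

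*Protocol article*

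**What the plan says.** Under Analysis of Behavioral and Brain Outcomes the protocol article states: "We will use a modified intention-to-treat analysis of behavioral outcomes to minimize attrition-related bias". Membership is then defined so that "all participants who have completed at least one postbaseline assessment will be analyzed". The same paragraph chooses linear mixed-effects models partly because the method "is resistant to missing values".

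PRE is part of the response in these models. Time has "three levels: PRE/POST2/POST4" for the two proximal composites and "5 levels: PRE/POST1/POST2/POST3/POST4" for the complex working-memory tasks. After a significant interaction, each training group's POST2 and POST4 scores are compared with its own PRE score, and the training groups are compared with the quiz group at POST2 and POST4.

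According to Procedure and Table 1, the cognitive PRE measures are taken at V1 and randomisation is at V2. The first postbaseline assessment is POST1 (after session 3) for the complex tasks and POST2 (between sessions 6 and 7) for the proximal composites. Sample Size assumes 10% to 16% attrition overall and does not say when it occurs.

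**The concern.** The rule removes people after randomisation, and their PRE scores are already in hand. A mixed model with PRE as a response level can use those scores: under missing-at-random they correct the POST mean for selection on PRE. A set adopted to limit attrition bias therefore gives up a protection that the chosen model already offers.

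Two kinds of contrast are exposed, under different conditions:

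- **Within-arm PRE-to-POST change** is biased if early dropout depends on PRE, even when the dependence is the same in every arm.
- **Arm-by-time contrasts** are biased only if the dependence differs between arms in strength or rate. An identical mechanism cancels.

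A difference between arms is conceivable because the tasks differ (N-back with an accuracy gate, speeded Stroop-like exercises, a general-knowledge quiz). The article does not show that one is expected.

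**Working it through.** **Inputs from the article.** 90 randomised to three arms; attrition 10% to 16%; correlation r = .50 between occasions; about 27 per condition retained.

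**Assumptions.** 30 per arm, SD 1, no true effect, equal variances, and the dropout mechanisms stated below.

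**The plan's own figure.** 90 × 0.90 / 3 = 27.0 and 90 × 0.84 / 3 = 25.2, so 27 per condition is the 10% end. The article gives no figure for PRE-only losses.

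**Mechanism.** Let d be the mean PRE of the retained participants minus that of all randomised in an arm. With PRE-only rows kept, the likelihood estimate of the POST mean is the retained POST mean minus r·d. It follows that, with those rows dropped:

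- within-arm change is biased by −(1 − r)·d;
- the POST mean is biased by +r·d;
- the arm-by-time contrast is biased by −(1 − r)·(d₁ − d₀), which is zero when d₁ = d₀.

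If k of 30 are lost with mean PRE z-score −a, then d = k·a / (30 − k).

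**How many are lost early.** Attrition per arm is 30 × 0.10 = 3.0 to 30 × 0.16 = 4.8. Spread evenly over the four intervals between assessments, a quarter falls before POST1: 0.75 to 1.2 per arm. If the rule applies per outcome, half falls before POST2 for the proximal composites: 1.5 to 2.4 per arm.

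**Size by hand, with no PRE-related loss in the comparison arm.**

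- One lost at z = −1: 1/29 = 0.034; × 0.5 = 0.017 SD.
- One lost at z = −1.5: 1.5/29 = 0.052; × 0.5 = 0.026 SD.
- Two lost averaging z = −0.9: 1.8/28 = 0.064; × 0.5 = 0.032 SD. Two both at −1.5 would give 3/28 × 0.5 = 0.054 SD.
- Five lost (about 16%) averaging z = −1: 5/25 = 0.20; × 0.5 = 0.10 SD. With five high scorers lost from the other arm: 0.20 SD.

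**Simulation (20,000 trials per scenario, two arms of 30, logit of dropout linear in PRE, all losses before any post score).** Arm-by-time bias with PRE-only participants dropped:

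| Scenario | Bias (SD) |
|---|---|
| Dropout unrelated to PRE, 13% in each arm | 0.00 |
| Related to PRE equally, 13% in each arm | 0.00 |
| 10% vs 16%, same slope (−1) | −0.03 |
| 8% related to PRE (slope −1) vs 5% unrelated (half the attrition early) | −0.035 |
| 13% in each arm, related to PRE in one only (slope −1) | −0.06 |
| 16% related vs 10% unrelated, slope −1 / −2 | −0.07 / −0.11 |
| 16% in each arm, opposite slopes (±1) | −0.14 |

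Stronger opposite selection, with dropout weights exp(∓1.5·z), gives about −0.2. Between-arm contrasts at the last post visit shift by a similar amount in the opposite direction. With PRE-only rows kept, the bias in the arm-by-time contrast lies between −0.005 and +0.001 throughout.

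**Within-arm change, all losses early.** −0.05 to −0.07 SD at 10% loss and −0.07 to −0.11 SD at 16%, for slopes −1 to −2.

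**Scale.** The SD of a change score is √(2 × 0.5) = 1, so with 27 per arm the standard error is √(2/27) = 0.27. The simulation gives about the same with or without the PRE-only rows. A bias of 0.03 is about a tenth of this (0.03/0.27 = 0.11), and 0.10 is just over a third (0.37).

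**The case against.** The plan labels its set as modified and discloses the rule. Compared with a completers-only analysis, the rule does reduce attrition bias. Read as written, any postbaseline assessment qualifies a participant, so someone with POST1 alone stays in and already supplies a PRE-only row to the proximal models. Only those lost in roughly the first week would then be excluded. Participants were blind to condition, and all arms had the same number of half-hour sessions in supervised small groups, which makes arm-specific dropout less likely. Sensitivity sets may be in an analysis plan that is not shown. The remedy also relies on missing-at-random given the observed scores: dropout driven by frustration during training is not repaired by PRE rows.

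Most of this stands, and it limits the size of the problem. It does not defend the exclusion, because the excluded scores exist, the model accepts them, and using them costs no precision.

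A reader might infer that any link between dropout and PRE biases the group comparison. That is true of within-arm change only. A reader might also take 0.1 to 0.2 SD as the expected bias. Those values need all attrition to precede any post score. The stronger opposite-selection case further needs someone 1 SD below the mean to be about 20 times (exp(3)) as likely to leave as someone 1 SD above, with the reverse in another arm. The documents support neither condition.

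**Conclusion.** The point holds as a low-priority inefficiency in the definition of the analysis set. The rule works against its own stated purpose, but the likely consequence is small: about 0.02 to 0.03 SD in an arm-by-time contrast with one or two early losses per arm, and about 0.035 SD if half the attrition is early. As a worst case it is about 0.1 SD, or 0.2 SD with opposite selection. All of these stand against a standard error of about 0.27. The bias is zero if dropout is unrelated to PRE. For arm-by-time contrasts it is also zero if dropout is related to PRE in the same way and at the same rate in each arm.

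These figures rest on 30 per arm, r = .50, and assumed dropout timing and selection, none of which the article gives except r. Nor does the article say whether the postbaseline requirement applies per outcome, which decides how many people the rule removes.

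The documents do not support the inference that the rule would manufacture a training benefit. If low scorers leave a training arm, the change contrast moves against training, while the comparison at POST moves in its favour.

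**What to change.** State that all randomised older adults with any score on the outcome, including PRE only, enter the mixed model for that outcome, with PRE as a level of time. Keep the present set (at least one postbaseline assessment) as a sensitivity analysis, and say whether that requirement is applied per outcome or across outcomes.

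The cost is a sentence or two of wording. The PRE scores are already collected, and the standard error is essentially unchanged (about 0.27 either way). The gain depends on missing-at-random given the observed scores.

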### Objectives

The general goal of the study is to compare 2 process-based interventions, inhibition and updating WM training, and assess their effect on the cognition and brain of cognitively healthy older adults relative to an active control condition. There are 6 objectives to the study: (1) measure the gains on the trained tasks; (2) determine transfer of gain on (i) proximal measures that are not trained directly but reflect the trained process, (ii) complex WM measures, and (iii) virtual reality tasks designed to reflect WM in real life; (3) identify the effect of WM training on cortical thickness and task-related brain activation in regions known to be involved in updating or inhibition or both; (4) assess whether cognitive (eg, pretraining cognition), psychosocial (lifestyle, education, motivation), and biological markers (eg, white matter lesions, sex, genotype) moderate the effect of training on cognitive and brain outcomes; (5) examine dose effects by measuring training, transfer, and cerebral outcomes at different time points; and (6) assess if training reduces the age-related deficit on cognitive and cerebral measures.

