### Hypotheses

It is hypothesized that older participants enrolled in WM training will show larger cognitive gains than those in the active control condition, and that gains will be specific to the cognitive process trained. We expect brain changes to be observed in regions that are associated with the trained process, with an overall decrease in activation due to improved neural efficiency for both functional magnetic resonance imaging (fMRI) tasks. It is expected that both trainings improve brain and performance parameters in older adults, which will increase to the levels of younger adults. Finally, it should be possible to identify individual factors that moderate the magnitude of the effect. The intervention may especially benefit participants with less advantageous cognitive and genetic profiles. However, these participants may require additional training for the intervention to be effective [26].

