### Effect on the Trained Tasks

The improvements on the trained tasks will be reported using inverse efficiency scores (IESs) for each participant, which corresponds to the mean of the reaction time per session divided by the proportion of error minus one. These scores will be calculated for the 1-, 2-, and 3-back blocks separately for the updating training and separately for congruent and incongruent blocks for the inhibition training.

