#### Analysis of Dose Effects

Dose effect will be analyzed with unconditional and conditional growth models to estimate and model the changes in behavioral and brain outcomes as training progresses.

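### The session 6 and 12 versus session 1 gain contrasts on the trained tasks depend on a session × condition interaction that does not ask whether there is a gain

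*Protocol article*

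**What the plan says.** In the Protocol article, the first objective under Objectives is "1) measure the gains on the trained tasks". The section Effect on the Trained Tasks sets the outcome: "The improvements on the trained tasks will be reported using inverse efficiency scores (IESs) for each participant". The scores are calculated separately for each N-back level or for congruent and incongruent blocks.

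Analysis of Behavioral and Brain Outcomes gives the test: "Training improvements will be tested using IES as the dependent variable with 2 separate analyses using". The factors are session, with 12 levels, and condition, with three levels for updating and two for inhibition. Each model contains one training arm, and condition means the task level, not the randomised group. The follow-up rule is: "When significant interaction effects are found, pairwise comparisons will be computed within each training group (comparing performances at sessions 6 and 12". The reference for those comparisons is session 1, and the rule adds comparisons between task conditions at the same two sessions.

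Two other statements bear on the point:

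- The paragraph on proximal outcomes in the same section has a fallback: "we will also conduct LMM analyses in the absence of interaction to make a direct comparison between the performances of the general knowledge training group". The other side of that comparison is the updating or the inhibition arm.
- The section on dose effects has a further analysis: "Dose effect will be analyzed with unconditional and conditional growth models to estimate and model the changes in behavioral and brain outcomes". It follows change over the course of training.

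**The concern.** The same follow-up rule is used for two kinds of model in which the interaction means different things. In the proximal-outcome models (time by training group) the interaction is the treatment effect, so it is a sensible condition for pairwise follow-up. In the trained-task models (session by task condition) it asks whether improvement differs between N-back levels, or between congruent and incongruent blocks. Objective 1 does not ask that. Nor do the Hypotheses, which predict that "older participants enrolled in WM training will show larger cognitive gains than those in the active control condition" and that gains are specific to the trained process.

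A participant who becomes faster by the same amount at every task level contributes nothing to the interaction. The comparisons of sessions 6 and 12 with session 1, which say how much was gained by mid-training and by the end, would then be skipped just when the gain is general. The follow-up between task conditions is properly tied to the interaction; the follow-up against session 1 is not.

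**Working it through.** **Reading the passages together.** The rule for a non-significant interaction compares the trained arms with the quiz arm. The trained-task models contain no quiz arm, so that rule cannot apply to them. The growth models address Objective 5 and do not supply the session 6 and session 12 contrasts. The follow-up rule on the trained tasks therefore stands without a fallback.

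**Inputs from the document.** About 27 participants per arm (Sample Size; 90 × 0.90 / 3 = 27), 12 sessions, 2 or 3 task conditions, α = .05. The plan gives no power figure for the trained-task models. Its one stated figure (0.80 for f = 0.15 with 3 repeated measures) concerns another design and is not used here.

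**Assumptions, not in the document.** Total SD of 1; linear gain from session 1 to session 12 of 0.3, 0.5 or 0.8 SD. Variance model A: 0.5 between participants and 0.5 residual. Variance model B: .5/.1/.4, read as participant, participant by condition, and residual.

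**Step 1: how often the interaction triggers the contrasts under equal gain.** The true interaction is zero, so a 5% test is significant about 5% of the time whatever the gain. Simulation under model A (4000 runs per case) gave 4.5% to 5.4%.

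**Step 2: session 12 versus session 1, averaged over C conditions.** The standard error is √(2σ²/(27·C)), with σ² the residual variance, and power is approximately Φ(gain/SE − 1.96). Under model A:

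- C = 2: SE = √(2 × 0.5/54) = 0.136. For 0.3 SD, 0.3/0.136 = 2.20 and Φ(0.24) ≈ .60. For 0.5 SD, 0.5/0.136 = 3.67 and Φ(1.71) ≈ .96.
- C = 3: SE = √(2 × 0.5/81) = 0.111. For 0.3 SD, 0.3/0.111 = 2.70 and Φ(0.74) ≈ .77.

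The simulation agrees, and shows what the rule and the main effect do (model A):

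| Conditions | Gain (SD) | Contrast, always computed | Contrast, only after significant interaction | Session main effect (11 df) |
|---|---|---|---|---|
| 2 | 0.3 | 59.4% | 2.9% | 58.7% |
| 2 | 0.5 | 95.9% | 5.1% | 98.7% |
| 2 | 0.8 | 100% | 5.0% | 100% |
| 3 | 0.3 | 76.8% | 3.5% | 80.3% |
| 3 | 0.5 | 99.5% | 4.7% | 99.9% |
| 3 | 0.8 | 100% | 4.5% | 100% |

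Under model B with two conditions, the always-computed contrast has power of about .67, .98 and 1.00, and the session main effect about .72, .997 and 1.00.

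**Step 3: unequal gain.** Under model B the interaction noncentrality is 27 × Σ(gain deviation)² × (143/121)/0.4, where 143/121 is the sum of squared deviations of a linear 0-to-1 trend over 12 sessions.

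- 0.3 v 0.6 SD: 27 × (2 × 0.15²) × 1.182/0.4 = 3.6 on 11 df
- 0.5 v 1.0 SD: 27 × (2 × 0.25²) × 1.182/0.4 = 10.0 on 11 df
- 0.2/0.5/0.8 SD: 27 × (2 × 0.3²) × 1.182/0.4 = 14.4 on 22 df

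The interaction is significant in about 18% of trials for the first pattern and in about half for the other two, a range of about 18–55%. Even then, the contrasts depend on a different question.

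**The case against.** The strongest reply is that a uniform gain is still tested. The plan says training improvements will be tested in a session-by-condition model, and such a model ordinarily reports a session main effect. The interaction clause governs only the pairwise follow-up. Step 2 bears this out: the main effect detects a uniform gain about as well as the direct contrast. The growth models carry no such condition, and Objective 5 includes training outcomes; if the gain is linear, a slope test under model B has power of about .95, 1.00 and 1.00. Inverse efficiency scores are also to be reported per participant whatever the tests show. All of this stands. A reader might infer that a uniform gain is tested nowhere, but the document does not support that.

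A reader might also infer that contrasts computed only after a significant interaction are distorted by selection. For the contrast averaged over conditions this does not hold. In a balanced design under these variance models it is independent of the interaction, and the rates in Step 2 are about the product of the two: 0.045 × 0.768 = 0.035 for three conditions and 0.3 SD. Selection could affect only contrasts within a single condition.

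It is also fair that the 5% figure follows almost by definition from an interaction of exactly zero, and that the document does not say equal gain is likely. Step 3 therefore gives the range for unequal gain.

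Finally, an article may leave to an analysis plan the naming of the main effect as the test. That is why the point rests on the rule that is stated, not on the omission. None of these replies supplies the session 6 and session 12 contrasts when the interaction is not significant.

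**Conclusion.** The point holds in a limited form. The planned gain contrasts on the trained tasks depend on a test that does not address Objective 1, and no stated fallback fits these single-arm models. They would be computed in about 5% of trials if gain is equal across task levels, and in about 18–55% under the three unequal patterns assumed. Gain would still ordinarily be detected, by the 11-df session main effect or the growth models. The loss is the planned, directional estimate of gain at mid-training and at the end, because the omnibus main effect has no direction and locates nothing.

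The 5% figure rests only on equal gain. The power figures and the 18–55% range also rest on the assumed gains, linear shape and variance splits.

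Severity is minor to moderate: the primary outcomes are the proximal composites, and the trained-task models support no comparison between arms.

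**What to change.** Replace the follow-up rule for the trained-task models with three statements:

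1. The session effect is the test of Objective 1 in each trained-task model.
2. Session 6 v 1 and session 12 v 1, averaged over task conditions, are planned contrasts, estimated with confidence intervals whatever the interaction shows, with multiplicity control over the two.
3. The session × condition interaction is kept as the separate test of whether gain depends on load or congruency, and contrasts by condition follow it when it is significant.

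The rule for the proximal-outcome models need not change for this reason. The cost is a few lines of text: same models, same data, two planned contrasts per training arm. The document reports data collection complete and analysis begun, so the change should be dated and described as made at that stage.
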